## Abstract

**Objective:**

Elderly individuals in long-term care facilities (LTCFs) have a higher prevalence of sarcopenia than those in the community. Exercise is the gold standard for preventing and treating sarcopenia. Regarding exercise, multicomponent exercises, including progressive resistance training (PRT), are beneficial. However, developing routine, structured exercise programs for the elderly in LTCFs is difficult because of a shortage of healthcare providers, particularly in rural regions. Exergame-based exercises can increase a player’s motivation and reduce staff time for an intervention. Nintendo Switch RingFit Adventure (RFA) is a novel exergame that combines resistance, aerobic, and balance exercises. In this study, we aim to investigate the clinical effectiveness of RFA on muscle and functional performance parameters among the elderly in LTCFs.

**Methods:**

The EXPPLORE (using **EX**ergame to **P**revent and **P**ostpone the **LO**ss of muscle mass, muscle strength, and functional performance in **R**ural **E**lders) trial is a single-center randomized controlled trial involving elderly individuals (≥60 years) living in LTCFs in rural southern Taiwan. The participants will be equally randomized to the intervention group (exergame-based exercise plus standard care) or the control group (standard care alone). Both groups will receive standard care except that the intervention group will receive exergame-based exercises at the time previously scheduled for sedentary activities in the LTCFs. The exergame-based exercise will be performed using RFA in the sitting position with a specialized design, including arm fit skills and knee assist mode. Each session of the exercise lasts 30 mins and will be performed two times per week for 12 weeks. The primary outcomes will be the osteoporotic fracture index, appendicular skeletal muscle mass index, dominant handgrip strength, and gait speed. Meanwhile, the secondary outcomes will be the dexterity and agility, muscle strength and thickness, range of motion of the joints of the dominant upper extremity, Kihon checklist, Medical Outcomes Study 36-Item Short-Form Health Survey, and Brain Health Test.

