### Selection of participants

All individuals, who participate regularly in LTCFs, including daycare centers and nursing homes, in rural regions of Kaohsiung City, southern Taiwan, will be eligible for study participation. The inclusion criteria are as follows: individuals (a) aged ≥60 years, (b) those living or participating in LTCFs for at least 1 month, (c) those who can understand and speak Chinese or Taiwanese, (d) those with sufficient cognitive capacity (judged by the researchers) to give informed consent and participate in the exergame-based exercise and data collection, and (e) those who can sit for more than 50 min for training and can complete the measurement of gait speed. (a) Individuals who have significant cardiopulmonary diseases, (b) those who regularly receive oxygen supplementation, (c) those who have uncontrollable hypertension, and (d) those who had a recent infection or fracture or were diagnosed with other diseases that might prohibit them from participating in exercises according to the guidelines of the American College of Sports Medicine will be excluded from this study (43). Participants in the intervention group will receive standard care with the exergame-based exercise for 12 weeks, whereas those in the control group will receive standard care routinely applied in LTCFs as usual. We will replace the scheduled sedentary activities in the LTCFs, such as singing, table games, and gardening, with the exergame-based exercise in the intervention group. Meanwhile, participants in the control group will perform the aforementioned sedentary activities in the LTCFs as usual. Therefore, the time for activities in the two groups will be the same. In addition to the exergame-based exercise and standard care, all participants will perform the usual traditional rehabilitation provided by therapists at the LTCFs.

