### Randomization

We will use sequentially numbered, opaque, sealed envelopes containing a group assignment number created by a person who is not clinically involved and, therefore, could be blinded to this study. Participants who fulfilled the inclusion and exclusion criteria will be equally randomized to the intervention and control groups with an allocation ratio of 1:1.

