### Contents of standard care (control group)

The standard care in the control group will be applied as usual in our LTCFs, in the way of group activities, including calisthenics (that could be performed in the sitting position), horticultural therapy, and group static activities (e.g., tabletop games). The programs will be performed two times per week for approximately 30–60 min, depending on the activity, and will be led by a therapist.

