### Quantitative data

We will use Statistical Package for the Social Sciences for Windows (version 19.0; Released 2010; IBM Corp., Armonk, NY, USA) for all statistical analyses. Continuous data are expressed as means with SDs, and categorical variables are presented as absolute numbers or percentages. The normality and homoscedasticity of the data will be checked before each analysis. For comparisons of demographic data between the experimental and control groups, the chi-square test, independent *t*-test, and Mann–Whitney *U*-test will be used as appropriate depending on the features of distributions of the data. As for the training effects on outcomes, a mixed analysis of variance, with time as a within-subject factor and intervention as a between-subject factor, will be performed. *Post hoc* analysis will be performed using the Bonferroni test. *P*-values < 0.05 will be used to indicate statistical significance. If both the data and the residuals are not normally distributed for ANOVA, we will use bootstrapping to get confidence intervals and use those to determine whether effects are statistically significant, rather than using *p*-values directly.

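### The trial is labelled single-center but recruits from several facilities of two types, and its stated model has no facility-type term: a minor loss of precision and protection against chance imbalance, not a bias

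*Protocol article*

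**What the plan says.** The Abstract (Methods) states that the trial "is a single-center randomized controlled trial". Selection of participants draws on individuals "who participate regularly in LTCFs, including daycare centers and nursing homes, in rural regions of Kaohsiung City". Contents of standard care says that the comparator "will be applied as usual in our LTCFs", again in the plural. The number of facilities is not given.

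Randomization describes numbered, opaque, sealed envelopes, with participants "equally randomized to the intervention and control groups with an allocation ratio of 1:1". It does not mention strata or blocks. Quantitative data specifies "a mixed analysis of variance, with time as a within-subject factor and intervention as a between-subject factor, will be performed". Neither facility nor facility type appears in that model.

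**The concern.** Two things do not fit together. A reader of the Abstract expects one site, while the eligibility text describes several facilities of two kinds. The model is then written as if there were one homogeneous site.

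Facility type could plausibly relate to how participants change over 12 weeks. The Background gives separate sarcopenia ranges for the two settings, and all participants also receive the usual rehabilitation from therapists at their own facility. If change differs by type, that difference goes into the error term, and a chance imbalance between arms is left uncorrected. With 26 per arm and 40% dropout expected, an imbalance would be hard to dismiss, and an adjustment added after unblinding would look chosen after the fact.

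**Working it through.** **Inputs from the article.** 52 participants, 26 per arm; 18 per arm before the dropout allowance; f = 0.4, power 80%, alpha 5% (Sample size calculation); three evaluations (Outcomes measured).

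**The plan's own figure.** With λ = f²·N·m / (1 + (m − 1)ρ), N = 36, m = 3 and ρ = 0.5 (assumed; the article gives none), λ = 0.16 × 36 × 3 / 2 = 8.64 and power is 0.815. N = 34 gives 0.791. So 18 per arm reproduces as a two-group, between-subject calculation with no facility term.

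**Assumptions.** Half the participants are of each type, and allocation is unstratified. Change differs by *d* between types, with *d* from 0 to 0.8 in units of the within-type SD.

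**1. Chance imbalance.** The number *k* of daycare participants in the intervention arm is hypergeometric. The imbalance between arms is |2k − n| / n, with n per arm.

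| n per arm | Imbalance | Smallest split counted | Probability |
|---|---|---|---|
| 26 | ≥ 15 points | 15 v 11 (15.4 points) | 0.406 |
| 26 | ≥ 20 points | 16 v 10 (23.1 points) | 0.165 |
| 18 | ≥ 20 points | 11 v 7 (22.2 points) | 0.318 |

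With 26 per arm the SD of the imbalance is 14.0 points.

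**2. Shift in the estimate.** A 23-point imbalance moves the unadjusted estimate by 0.231 × *d*: 0.06 SD at d = 0.25 and 0.18 SD at d = 0.8. The standard error without adjustment is at least √(2/26) = 0.277 SD, so even the larger shift is below one standard error.

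**3. Precision.** The unadjusted SD of the estimate is √(2/26 + d² × 0.140²). The SD adjusted for type is the root of the average, over allocations, of 26 / (2k(26 − k)), which is 0.280. With exactly balanced strata it is √(2/26) = 0.277.

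| *d* | Unadjusted | Adjusted for type | Change |
|---|---|---|---|
| 0 | 0.277 | 0.280 | 1.0% worse |
| 0.25 | 0.280 | 0.280 | 0.2% worse |
| 0.5 | 0.286 | 0.280 | 2.0% better |
| 0.8 | 0.299 | 0.280 | 6.3% better |

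At d = 0.8, stratification with adjustment gives 1 − 0.277/0.299 ≈ 7%.

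**4. Validity.** A simulation used 52 people, individual 1:1 randomization, 2, 4 or 6 equal-sized facilities, a facility variance share of 0 to 0.20 (assumed) and 4,000 runs per setting. Type I error without a facility term was 0.044 to 0.059.

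**5. Fixed terms for each facility.** The same simulation gave power for a 0.8 SD effect at a single endpoint. At a variance share of 0.20 with 2/4/6 facilities, it was 0.85/0.83/0.83 without a term, 0.87/0.86/0.85 with facility terms, and 0.87/0.88/0.88 with stratification as well. At a share of 0 to 0.05 there was no gain. With six facilities and a share of 0, facility terms without stratification lowered power from 0.82 to 0.75.

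**6. Which term is needed.** A between-subject main effect of type does not alter the within-subject test of intervention by time. Differences in change are absorbed only by type by time, which takes (2 − 1)(3 − 1) = 2 degrees of freedom.

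**The case against.** The strongest reply is that little of this is an error. The label may mean one coordinating center, and the Abstract sentence that uses it also mentions facilities in the plural. Strata and covariates are often left to a full protocol or analysis plan, and neither is shown. Silence in the Randomization section is therefore not evidence of unstratified allocation; that is an assumption here, and the reply stands. The label and the stated two-factor model, however, are in the text.

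A reader might also infer that standard care differs by facility. The article does not say so: it describes one therapist-led programme twice weekly and ties the variation in session length to the activity. Nor does it say that daycare and nursing-home participants differ in dependency. The sarcopenia ranges for the two settings overlap (22–87.1% and 17.7–73.3%), and the same entry criteria apply to everyone. The 0.8 SD end of the range is also generous, since it makes facility type matter for change as much as the planned intervention effect (f = 0.4, or d = 0.8). The low end, with no gain, is just as compatible with the document.

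**Conclusion.** The point holds as a minor one. The label and the recruitment text need reconciling, and the stated model gives up a cheap protection.

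It would be tempting to conclude that omitting facility biases the treatment comparison, or that the trial needs a clustering correction. Neither follows. Individuals are randomized, so the comparison is unbiased, and simulated type I error stays near 5%. The intervention-by-time contrast also removes stable differences in level between facilities, so only differences in change matter.

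The cost is limited to chance imbalance (15 points or more in about 41% of allocations, 20 or more in about 16%) and a precision effect from none to about a 6–7% reduction in the SD of the estimate. These figures rest on an assumed 50:50 split of types, unstratified allocation and a 0 to 0.8 SD difference in change. The number and sizes of the facilities are not in the article.

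**What to change.** 1. Describe the trial as recruiting from multiple facilities under one coordinating center, or otherwise reconcile the label, and state the number and type of facilities.
2. If enrolment has not begun, and unless this is already planned, keep separate sealed-envelope sequences for daycare and nursing-home participants. If it has begun, change the model only.
3. Add facility type and facility type by time to the mixed ANOVA, prespecified before unblinding.
4. Do not add a fixed term for each of many small facilities, because this can reduce power.

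**Cost:** a second set of envelopes, one between-subject degree of freedom (error 50 to 49 with 52 participants) and two within-subject ones (error 100 to 98). No participants are added. If type is unrelated to change and allocation is not stratified, the SD of the estimate rises by about 1%.

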## Primary outcomes

The primary outcomes chosen for this study are the criteria for the diagnosis of sarcopenia proposed by the AWGS, including appendicular skeletal muscle mass index (ASMMI), dominant HGS, and usual gait speed. Moreover, the Study of Osteoporotic Fractures Index (SOF index), which indicates the frailty status, is also one of the primary outcomes.

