## Statistical analysis

### Sample size calculation

Since a high-quality study evaluating the effects of a similar intervention on muscle strength, physical activity, and function was unavailable when we wrote our protocol, we used previous results from one study using augmented reality (AR)-based exercise for one of our primary outcome measures (ASMMI) (72) for this power calculation. The effect size of a similar study for the AR-based intervention is high (0.71). Based on G*Power (version 3.1.9.2, for Windows), at least 18 observations in each group should be recruited by detecting a difference of 2 standard deviations (SD) of the ASMMI between the groups with a power of 80% and alpha of 5%, and the effect size is determined to be high (*F*-test family, 0.4) (73). To account for an expected dropout rate of 40%, given that most participants in the LTCFs have comorbidities, we decided to increase this number to a group size of 26. Thus, the aim will be to include at least 52 patients in the study.

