If the findings of this study show that the exergame-based exercise *via* RFA could improve the parameters of muscle and functional performance, the training method should be implemented as a treatment option for all older individuals living in LTCFs, particularly for those in rural regions with lesser healthcare resources. A successful exergame-based exercise would provide benefits beyond muscle strength, muscle mass, and ADLs of the elderly because it would also enhance the HRQoL or even help the elderly age gracefully. We expect that the protocol will be useful and practical to implement in real-world settings. With the positive results of this protocol, further larger studies could be conducted to examine whether the exergame-based exercise *via* RFA could be a treatment alternative to time- and manpower-consuming therapies currently applied in LTCFs.

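### Four unranked primary outcomes are each judged at P < 0.05 with no rule for how many must succeed, so the error rate is not held at 5% if any one of them counts as success

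*Protocol article*

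**What the plan says.** The abstract lists the primary set: "The primary outcomes will be the osteoporotic fracture index, appendicular skeletal muscle mass index, dominant handgrip strength, and gait speed". Table 2 labels the same four measures as primary. The Primary outcomes section explains that three are diagnostic criteria for sarcopenia and adds the SOF index, "which indicates the frailty status, is also one of the primary outcomes".  None of these places ranks them.

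The Quantitative data section prescribes a single mixed ANOVA model for judging whether the training works, specified as one "with time as a within-subject factor and intervention as a between-subject factor, will be performed". It then says of the post hoc stage that "analysis will be performed using the Bonferroni test", and sets a single criterion: P "< 0.05 will be used to indicate statistical significance". If normality fails, bootstrap confidence intervals take over the decision. No adjustment across outcomes is attached to either route.

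The sample size section spends the full 5% alpha on a calculation "for one of our primary outcome measures (ASMMI"), giving 18 evaluable per group at 80% power, raised to 26 per group for dropout.

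The discussion draws a consequence from favourable muscle and function findings: "the training method should be implemented as a treatment option for all older individuals living in LTCFs".

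**The concern.** With four primary outcomes, a 5% error rate for the trial's main claim needs either a rule for combining the tests or a split of the alpha. The protocol article gives neither and states a flat threshold. Followed as written, the plan lets a significant result on any one of muscle mass, grip strength, gait speed or frailty be reported as a positive primary finding.

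The Bonferroni sentence does not close this gap. It follows directly on the mixed analysis of variance and concerns post hoc comparisons, which are naturally pairwise comparisons within one outcome.

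At stake is how a split result would be read. If one primary outcome is significant and three are not, the plan does not say whether the trial succeeded, and a reader cannot attach a 5% error rate to a claim of success.

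**Working it through.** **Inputs from the protocol article.** Four primary outcomes (abstract, Table 2, Primary outcomes). Threshold 0.05 for each test (Quantitative data). Three evaluations (Outcomes measured). Effect size f = 0.4, alpha 5%, power 80%, 18 evaluable per group (Sample size calculation).

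**Assumptions, not in the document.** The correlation r between the four test statistics, taken as equal for all pairs, and the correlation ρ between repeated measurements of one outcome. These are different quantities.

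**1. The plan's own figure.** The planned 18 per group can be reproduced with the between-group test of a repeated-measures analysis of variance. The noncentrality is λ = f²·N·m / (1 + (m − 1)ρ), with 1 and N − 2 degrees of freedom.
- With f = 0.4, m = 3 and ρ = 0.5, N = 36 gives λ = 0.16 × 36 × 3 / 2 = 8.64 and power 81.5%.
- N = 34 gives λ = 8.16 and power 79.1%.
- So 36 in total, 18 per group, is the smallest even number reaching 80%. This is the power for one outcome tested at the full 0.05.

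**2. Family-wise error under an any-of-four reading, independent tests.** 1 − 0.95⁴ = 1 − 0.8145 = 0.185.

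**3. The same with correlation.** Four equicorrelated two-sided normal test statistics were simulated (1,000,000 draws), each tested at 0.05:

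| Assumed r | At least one false positive |
|---|---|
| 0 | 18.5% (exact) |
| 0.3 | 17.4% |
| 0.5 | 15.6% |
| 0.7 | 13.0% |
| 0.8 | 11.4% |
| 0.9 | 9.4% |
| 1.0 | 5.0% |

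The rate returns to 5% only when the four tests are in effect the same test.

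**4. All-four reading.** If every outcome had to be significant, the chance of a false claim could not exceed the 5% of any single test, so nothing is inflated.

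**5. After adjustment.** The first Holm step is 0.05 / 4 = 0.0125. With no true effects, the chance of any rejection is 1 − 0.9875⁴ = 4.9% under independence, and 3.7% at r = 0.7 by simulation.

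**6. Power cost.** In the model of step 1, tested at 0.0125:
- 36 evaluable: power 62%, against 81% at 0.05.
- 50 evaluable (25 per group): the smallest even total reaching 80%.
- 52 evaluable: power 82%. This is the whole recruitment target, so it would need no dropout.

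These power figures belong to the between-group test that reproduces the planned size. They do not carry over to a group-by-time test, for which the same f and ρ imply a different sample size (12 in total at 0.05).

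**The case against.** The strongest objection is that a journal article condenses a fuller protocol, and that rules for combining several primary outcomes are commonly left to an analysis plan. That stands for the missing success rule taken alone. It does not dispose of the point, because the article does more than stay silent: it fixes the threshold for all analyses and says where Bonferroni applies. A later plan would have to change that rule, not just add detail.

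Second, a reader might infer that the trial simply has a 13% to 19% false positive rate. The documents do not support that as a fact. It requires that any one outcome is enough and that the correlations lie between 0 and 0.7, and the article states neither. Nor do they support a larger figure based on counting both the group effect and the group-by-time effect as routes to success. The article does not say which is decisive, and it does not say that either would do.

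Third, a reader might infer that one chance result would trigger adoption in all facilities. The discussion is more guarded. Its condition refers to parameters in the plural, it speaks of a treatment option, it urges caution and limits generalisation to similar populations, and it proposes larger studies. The implementation sentence makes the undefined success condition more important, but it is not a decision rule.

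Fourth, the four outcomes were chosen for a stated reason, as criteria for sarcopenia and frailty. That justifies measuring all four. It does not say how four tests combine into one conclusion.

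**Conclusion.** The point holds in conditional form. The plan names four unranked primary outcomes, judges each at 0.05, confines Bonferroni to post hoc comparisons and states no success rule. If any one significant outcome counts as success, the family-wise error is 18.5% for independent tests and about 16%, 13% and 9% at assumed correlations of 0.5, 0.7 and 0.9. Even at 0.9 it is nearly twice the nominal level. Correlations that high seem unlikely for an impedance-based muscle index, grip force, walking speed and a three-item frailty index, but that is judgement. Under an all-four rule there would be no inflation. The defect is that the plan fixes the threshold without fixing which reading applies.

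**What to change.** In the Quantitative data section:

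1. Name one decisive between-group test for each primary outcome, for example the group-by-time effect from the planned mixed analysis of variance.
2. Apply Holm across the four resulting P values at a family-wise 5%. The smallest is compared with 0.0125, then 0.05/3 = 0.0167, 0.025 and 0.05, stopping at the first failure. Holm is valid whatever the correlations.
3. Define a positive trial as at least one Holm-significant primary outcome.
4. If bootstrap intervals replace P values, carry the same adjustment into them.

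Alternatively, the sponsor may designate one primary outcome of its choice and make the other three secondary. ASMMI is the one the sample size already rests on; any other choice would need its own power justification.

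**Cost.** Holm is more than a wording change. With 36 evaluable, first-step power under the step 1 model is 62% rather than 81%, and restoring 80% takes about 50 evaluable. The protocol should state this, and should redo the calculation for the named test if that is the group-by-time effect. A single primary outcome avoids the power loss. Changing the primary set would also need a protocol and registry amendment. Either change should be made before any unblinded analysis.
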